## Abstract

**Background:**

Midportion Achilles tendinopathy (AT) is a common overuse injury, usually requiring several months of rehabilitation. Exercise therapy of the ankle plantar flexors (i.e. tendon loading) is considered crucial during conservative rehabilitation. Alfredson’s isolated eccentric and Silbernagel’s combined concentric-eccentric exercise programs have both shown beneficial results, but it is unknown whether any of these programs is superior for use in clinical practice. Therefore, the primary objective of this study is to compare the effectiveness of both programs on clinical symptoms. Secondary objectives are to compare the effectiveness of both programs on quality of life and functional outcome measures, to investigate the prognostic value of baseline characteristics, to investigate differences in cost-effectiveness.

**Methods/Design:**

Eighty-six recreational athletes (21–60 years of age) with unilateral chronic midportion AT (i.e. ≥ 3 months) will be included in this multicenter assessor blinded randomized controlled trial. They will be randomly allocated to either a group performing the Alfredson isolated eccentric training program (*n* = 43), or a group performing the Silbernagel combined concentric-eccentric program (*n* = 43). In the Alfredson group, participants will perform eccentric heel-drops on their injured side, twice daily for 12 weeks, whereas in the Silbernagel group, participants perform various concentric-eccentric heel-raise exercises, once daily for 12 weeks. Primary outcome measure will be the Victorian Institute of Sport Assessment – Achilles (VISA-A) questionnaire. Secondary outcomes will be a visual analogue scale (VAS) for pain during daily activities and sports, duration of morning stiffness, global perceived effect, the 12-item Short Form Health Survey and the Euroqol instrument, and functional performance measured with the heel-raise test and the countermovement jump. Additionally, alongside the RCT, a cost-effectiveness analysis will be performed. Assessments will be performed at baseline and after 12, 26, and 52 weeks.

**Discussion:**

This study is the first to directly compare the Alfredson and the Silbernagel exercise program in a randomized trial. The results can further enlarge the evidence base for choosing the most appropriate exercise program for patients with midportion AT.

**Trial registration:**

Dutch Trial register: NTR5638. Date of registration: 7 January 2016.

## Background

Midportion Achilles tendinopathy (AT) is a common overuse injury of the lower extremity, [1, 2] most prevalent in male athletes who participate in sports that involve running and/or jumping. [2–4] When not adequately managed, the injury may cause long term absenteeism of sports and daily activities. [5] Treatment of midportion AT is initially conservative, usually requiring several months, with a plethora of possible treatment options. [6, 7].

Historically, AT is considered as an inflammatory condition, but more recently it has been regarded as a failed healing response of the tendon, with minimal inflammatory influence. [8, 9] In 2009, Cook and Purdam proposed a model that considers tendinopathy as a continuum, in which three somewhat interchangeable stages can be distinguished: 1) reactive tendinopathy, 2) tendon dysrepair, and 3) degenerative tendinopathy. [10] According to the authors, these stages all require tailored load management and exercise intervention strategies. The model was recently revisited, [11] but it is still generally agreed that exercise therapy (i.e. tendon loading) is crucial to promote improvement of symptoms and function. [3, 9, 12].

Several exercise programs have shown favourable results in mid-portion AT, with both beneficial effects on pain and function. Recent studies concluded that there is strong evidence for eccentric exercise therapy, [6, 7] particularly according to the Alfredson eccentric exercise program. [13] In the Alfredson program, the plantar flexor muscle-tendon unit is loaded eccentrically by performing heel drops on the injured side, while using the non-injured limb to (concentrically) return to the start position. [14] A total of 180 repetitions is performed daily, and this may be a great time-consuming burden for the patient, potentially compromising compliance and consequently the effectiveness of the program. Although the majority of studies using the Alfredson program reported significant improvements post-intervention, [14–17] it should be noted that other studies reported less positive effects. [18, 19] Moreover, a recent study of Stevens & Tan (2014) showed that a less stringent “do-as-tolerated” eccentric protocol can lead to equal improvements in pain and function compared to the Alfredson protocol, [20] which may be advantageous from a patient perspective. However, as exercises were performed only for a period of 6 weeks, and mid- and long-term follow-up measurements (i.e. > 6 weeks) were lacking, conclusions should be interpreted with caution.

Also, exercise programs other than isolated eccentric loading showed to be effective in AT. [21, 22] In a recent randomized controlled trial (RCT), Beyer et al. [23] found that heavy slow resistance training (HSRT) using gym equipment leads to equally good clinical improvement compared with the Alfredson program. Furthermore, in an earlier systematic review, Malliaras et al. [24] already concluded that there is equivalent evidence for the Silbernagel concentric-eccentric exercise program, although this conclusion was based on limited evidence. Unlike the Alfredson protocol, the Silbernagel protocol also comprises concentric and even plyometric loading of the Achilles tendon. [25, 26] From a patient perspective, a potential benefit of the Silbernagel program over the Alfredson program, may be the frequency of the exercises (i.e. only once a day). This may encourage training compliance and consequently can result in better outcomes. Furthermore, a combination of concentric and eccentric loading may better restore concentric muscular deficits, as training gains are known to be specific to the contraction mode. [27].

Although both the Alfredson and Silbernagel program have shown favorable results in midportion AT, [14, 16, 17, 25, 26, 28, 29] comparison of the results is hampered by heterogeneity of study populations. [13, 24] Insight into whether one of these programs is superior may lead to better results in the management of patients with AT.

This article provides a detailed description of the study design, target population, and methods/procedures of a pragmatic multicenter RCT that will investigate differences in effectiveness between the Alfredson and Silbernagel exercise program for patients with midportion AT.

### Study objectives

The primary objective of this study is to compare the effectiveness in terms of symptom reduction and function of the Alfredson isolated eccentric exercise program to the Silbernagel concentric-eccentric exercise program after 12 months in patients with chronic midportion AT.

Secondary objectives are 1) to investigate differences in effectiveness on global perceived effect and quality of life (QOL), 2) to investigate differences in effectiveness on functional outcome measures, and 3) to investigate the prognostic value of baseline characteristics. Furthermore, alongside this RCT, a cost-effectiveness evaluation between both programs will be performed.

## Methods/Design

### Study design and setting

This protocol was developed in accordance with the SPIRIT guidelines, [30] and describes an assessor blinded multicenter parallel-group RCT, with a one-year follow-up. The study will be conducted in two different centers, i.e. the University Medical Center Utrecht (UMCU, department of Rehabilitation, Physical Therapy Science & Sports), Utrecht, The Netherlands, and Papendal Sports Medical Center, Arnhem, The Netherlands. Participants will be randomized to a group performing either the Alfredson isolated eccentric or the Silbernagel combined concentric-eccentric exercise program. Randomization will be performed using a web-based randomization system, and allocation will be concealed. The investigators who are involved in baseline and follow-up measurements, and data analysis will be blinded to group allocation.

Measurements will be performed at baseline, and after 12, 26, and 52 weeks follow-up (see Fig. 1). The study protocol is in accordance with Declaration of Helsinki, and has been approved by the ethics committee of the UMCU (registration number 16–158). The protocol was registered with the Dutch Trial Register on 7 January 2016 (NTR5638). Written informed consent will be obtained from all participants prior to their participation.

**Fig. 1 Fig1:**
[figure not shown]
Flow chart of the study design

### Participant selection

Recreational athletic patients (both male and female) with a clinical diagnosis of unilateral midportion AT, characterized by activity-related Achilles tendon pain and swelling at 2 to 7 cm from the calcaneal insertion, [31] are eligible for inclusion if they meet the following inclusion criteria: 1) 18–60 years of age, 2) duration of symptoms of at least 3 months, 3) participating in sports involving Achilles tendon loading (i.e. sports characterized by walking, running and/or jumping), and 4) able to comply with both exercise programs.

Participants are excluded in case of: 1) bilateral symptoms, 2) diagnosis of insertional AT, 3) washout period of <4 weeks from other treatments for their AT, 4) corticosteroid injections in the region of the Achilles tendon in the previous 12 months, 5) other lower limb injuries of the affected limb in the previous 12 months, 6) musculoskeletal surgery of the affected limb in the previous 12 months, 7) history of Achilles tendon rupture in the affected limb, or 8) systemic diseases, such as rheumatoid arthritis or diabetes mellitus.

### Sample size calculation

Sample size was calculated based on two high quality RCTs having investigated the Alfredson program and the Silbernagel program respectively, and using the VISA-A questionnaire as their primary outcome measure. [16, 26] We used the respective change (mean ± standard deviation [SD]) in VISA-A scores for the groups that followed the above-mentioned exercise programs:Rompe et al. [16] (*n* = 25): VISA-A Δ 22.4 ± 19 for the Alfredson programSilbernagel et al. [26] (*n* = 19): VISA-A Δ 34 ± 17 for the Silbernagel program

This resulted in an expected effect size of 0.64 between both exercise programs, with an expected VISA-A change score that exceeds the minimal clinically important difference of 10 points. [23] Using G*Power 3.1, and assuming α two-sided = 0.05 and a power of 0.80, a total of 39 participants in each study arm was required. The dropout rate in the above-mentioned studies was 4% [26] and 9% [16] respectively. We chose to take the most conservative dropout rate of 9% into account, resulting in a required amount of 86 in total, i.e. 43 participants in each arm.

### Recruitment and informed consent

Primarily, participants are recruited from the patient population of the two afore mentioned centers. Secondary, general practitioners and orthopedic surgeons in the surroundings of Papendal Sports Medical Center (Arnhem, The Netherlands), will be asked to identify participants.

Eligible participants will be informed about the study by their treating (sports) physician or physiotherapist through an information letter, and they will initiate contact with the coordinating investigator (BH). Eligibility criteria of these participants will initially be checked by telephone, and subsequently, if they meet the criteria, an appointment is made for baseline assessment. Prior to baseline assessment, eligibility criteria will be confirmed and participants will sign informed consent.

### Randomization procedure

Randomization will be performed directly after baseline assessment, by an independent secretary using a computer-generated random sequence table. Eighty-six envelopes will be prepared with a description of the allocated intervention (i.e., Alfredson or Silbernagel program). These envelopes will be sealed, and then shuffled and sequentially numbered. After baseline assessment, the secretary will pick an opaque sealed envelope according to the randomization table. Subsequently, within 1 week participants will be referred to one of the supervising physiotherapists, who is informed about the allocated program by the independent secretary. During the first session, participants will receive detailed instructions on the allocated exercise program.

The randomization code will not be broken until the final follow-up measurement has been performed (i.e. participant’s last visit), and data analysis has been completed. Participants are instructed not to reveal their group allocation to the investigator during all measurement procedures.

### Intervention

One study arm performs the Alfredson isolated eccentric exercise program, [14] which comprises 12 weeks of eccentric heel-drops on the injured limb, with the use of the uninjured limb to concentrically return to the start position. Exercises are performed twice daily, for three sets of 15 repetitions, both with a straight and bent knee (i.e. 180 repetitions each day). Non-disabling pain during the exercises is permitted, and load is added gradually in a backpack (in steps of 5 kg) when exercises can be performed without pain.

The second study arm performs an exercise program according to the Silbernagel protocol. [25, 26] This program comprises various concentric and eccentric heel raise exercises, which are performed both on two legs and one leg, with three sets of 15 repetitions. The duration of the program is also 12 weeks, and non-disabling pain during the exercises is also permitted, but contrary to the Alfredson program, exercises are performed only once daily. Progression is made by changing from bipedal to unipedal exercises, by progressing from concentric-eccentric to purely eccentric loading, by adding weight in a backpack (in steps of 5 kg when pain did not exceed 5 on a 0–10 numerical rating scale), and finally by using fast-rebounding and plyometric exercises.

Table 1 depicts the key features of both exercise programs. The timing of the exercise as well as the time under tension are not described, as we wanted to replicate the clinical prescription of the exercise programs.

**Table 1 Tab1:** Key features of the exercise programs

	Alfredson	Silbernagel
Duration of exercise program	12 weeks	12 weeks
Frequency of exercises	Twice daily	Once daily
Amount of exercises	2	4–5
Sets and repetitions	3 × 15	3 × 15
Exercise mode	Slow isolated eccentric	Concentric, eccentric, plyometric
Pain tolerated	Non-disabling pain	Not more than 5 on a 0–10 NRS
Progress	No pain	Phase 1–2 – 3
Progression	Add load (5 kg)	Add load (5 kg)

*NRS* numerical rating scale

The content of both programs will be instructed in detail by the supervising physiotherapists during the first appointment. Participants will perform all exercises from both programs at home. After two and 6 weeks of training, an appointment with the supervising physiotherapist is made to discuss potential difficulties with the exercises and adjust load when possible.

During the intervention period, participants are asked to refrain from other treatments and from anti-inflammatory medication related to their injury. If they receive other (medical) treatments after the intervention period, they are asked to register this in a logbook.

Participants in both study arms are advised not to participate in any tendon loading sports activities (i.e. walking, running and jumping) during the first 3 weeks of the intervention period. [23] Subsequently, they are allowed to resume tendon loading sports activities, as long as pain does not exceed 50 mm on a 0–100 mm visual analogue scale (VAS), and pain subsides within 24 h after the activity. [26].

### Education and monitoring

The research team will organize an information meeting in order to inform the involved physiotherapists of the two participating centers about the study procedures, their exact role, and the content of the exercise programs. During this meeting, written information is also provided. For potential referrers, an information letter will be sent by the coordinating investigator. In this letter, the objectives of the study and a short description of the study design are described.

Monitoring of study procedures will be performed by an independent monitor during multiple visitations. These include an inspection of the study file for each center prior to the start of the study, and a check of the procedures and study files after 1 year and at the end of the study.

### Outcome measures

#### Baseline assessment

During baseline assessment – besides the primary, secondary and other outcome measures – demographic and anthropometric characteristics such as age, weight, height, body mass index, job type and activity level, sport type and activity level, and referral type are recorded using a standardized questionnaire. Additionally, waist circumference will be recorded with a flexible tape measure, [32] range of motion for ankle dorsiflexion will be recorded using the weight bearing lunge test, [33] and dorsiflexion range of motion of the first metatarsophalangeal joint will be measured with a standard goniometer. [34] Body weight and sport activity level will also be recorded at T1, T2 and T3, as these variables are thought to vary throughout the study period and thus may potentially influence the study outcome.

#### Primary outcome measure

The primary outcome for this study will be the difference in VISA-A scores between both programs after 12 months. The VISA-A questionnaire has been shown reliable and valid for evaluating clinical severity of symptoms of AT, [35] and was recently translated/validated in Dutch. [36] It consists of eight questions, covering the three domains of pain, and function in daily living and sporting activities. Scores range from 0 to 100, where 100 represents a perfect function.

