### Measurements

All measurements will be conducted at baseline (T0), at 12 weeks (i.e. termination of intervention, T1), 26 weeks (T2), and at 52 weeks (T3) follow up, and include both the afore mentioned questionnaires and physical examination. Participants can complete the questionnaires online (secured environment), by using a hyperlink that will be sent to them by e-mail. All physical assessments are conducted by the same investigator (BH), who is blinded to group allocation. For a detailed overview of all outcome measures collected in the course of the study and the respective follow-up times, see Table 2.

**Table 2 Tab2:** Overview of outcome measures collected in the course of the study

	*Baseline*	*12 weeks*	*26 weeks*	*52 weeks*
Eligibility criteria check	*X*			
Body height	*X*			
Body weight	*X*	*X*	*X*	*X*
BMI	*X*			
Job type & activity level	*X*			
Sport type & activity level	*X*	*X*	*X*	*X*
Referral type	*X*			
Waist circumference	*X*			
Dorsiflexion ROM ankle	*X*			
Dorsiflexion ROM first MTPJ	*X*			
VISA-A score	*X*	*X*	*X*	*X*
VAS for pain during sport and daily activities	*X*	*X*	*X*	*X*
Morning stiffness	*X*	*X*	*X*	*X*
Global perceived effect (7-point scale)	*X*	*X*	*X*	*X*
Quality of life (SF-12 and EQ-5D)	*X*	*X*	*X*	*X*
Functional performance (CMJ and heel raise test)	*X*	*X*		*X*
Variables related to cost-effectiveness: - Medical consumption - Absenteeism from (un)paid work - Absenteeism from school - Absenteeism from sports activities	*X*	*X*	*X*	*X*
Compliance to exercise program		*X*		
Isometric strength of hip musculature	*X*	*X*		*X*

*BMI* body mass index, *ROM* range of motion, *MTPJ* metatarsophalangeal joint, *VISA-A* Victorian Institute of Sports Assessment – Achilles, *VAS* visual analog scale, *SF 12* 12-item short from health survey, *EQ-5D* Euroqol instrument, *CMJ* countermovement jump

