### Statistical analyses

Differences between the Alfredson and Silbernagel group will be analyzed according to intention-to-treat (ITT) principle. If necessary, missing data will be imputed using multiple imputation. Descriptive statistics will be calculated for all continuous variables, and means and SDs will be reported (or median and interquartile range for non-parametric data). For nominal and categorical data, proportions will be calculated and reported.

Baseline comparability of the two groups will be assessed by the Student t-test (parametric data), and non-parametric tests where appropriate. To assess differences in (pseudo)metric data within and between the groups over time, an analysis of variance (ANOVA) will be performed, with post-hoc tests to correct for multiple testing. Multivariate regression techniques will be conducted to model the prognostic value of baseline variables on outcome. The cost-effectiveness will be estimated by calculating the incremental cost-effectiveness ratio: (costs of Silbernagel program – costs of Alfredson program) / (health benefit of Silbernagel program – health benefit of Alfredson program), and will be expressed as costs per quality adjusted life year (QALY).

All analyses will be performed with statistical significance level set at α = .05 (two-sided).

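### No baseline VISA-A covariate is stated for the primary comparison, and baseline is tested for significance between randomised arms; adjusting for it would gain precision at no cost

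*Protocol article*

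**What the plan says.** Four parts of the protocol article bear on this.

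- **Primary outcome measure:** "The primary outcome for this study will be the difference in VISA-A scores between both programs after 12 months". Baseline VISA-A is not mentioned there.
- **Sample size calculation:** the planning is on change from baseline: "We used the respective change (mean ± standard deviation [SD]) in VISA-A scores". The Silbernagel input, for example, is "VISA-A Δ 34 ± 17 for the Silbernagel program".
- **Statistical analyses:** differences within and between groups over time are to be assessed so: "an analysis of variance (ANOVA) will be performed, with post-hoc tests to correct for multiple testing". No covariate is named. Baseline is dealt with by tests between the arms: "Baseline comparability of the two groups will be assessed by the Student t-test (parametric data), and non-parametric tests where appropriate". Baseline variables appear as regressors in one place only, for the prognostic objective: "Multivariate regression techniques will be conducted to model the prognostic value of baseline variables on outcome".
- **Measurements:** "All measurements will be conducted at baseline (T0), at 12 weeks", with further visits at 26 and 52 weeks. Table 2 marks VISA-A at all four visits. Under Randomization procedure, allocation follows directly after the baseline assessment, so the covariate should exist for every randomised participant.

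**The concern.** Baseline VISA-A is the same instrument as the endpoint, recorded before allocation, and so is likely to be prognostic for the 12-month score. The article places the comparison on two scales (12-month score in the outcome definition, change in the sample size) and names a model compatible with either. Neither scale uses baseline in the most efficient way. A comparison of 12-month scores ignores it. A comparison of changes subtracts it with a fixed coefficient of 1, whatever the data say. A model with baseline as covariate estimates that coefficient.

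The baseline significance tests do not fill the gap. After proper randomisation, any baseline difference arises by chance, so the tests examine a null hypothesis already known to be true. A non-significant result does not show that an imbalance is harmless, and no result of the test removes one.

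At stake is the precision of the primary estimate in a trial that expects about 39 evaluable participants per arm.

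**Working it through.** **Inputs.** From Sample size calculation: changes of 22.4 (SD 19) and 34 (SD 17), two-sided α 0.05, power 0.80, 39 evaluable per arm, 9% dropout, minimal clinically important difference 10 points. Assumed, because the article gives neither: the correlation r between baseline and 12-month VISA-A (0.3, 0.5, 0.7) and, at first, equal SDs at the two visits.

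**Step 1: the plan's own figure.** Difference = 34 − 22.4 = 11.6. Pooled SD of change = √((19² + 17²)/2) = 18.03. Effect size = 11.6/18.03 = 0.643. A two-sample t-test (non-central t) needs 38.9, so 39 per arm. Then 39/0.91 = 42.9, so 43 per arm and 86 in total. The stated figures reproduce.

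**Step 2: variances.** Let σ be the common SD of the score at each visit.

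- Final score: σ²
- Change: 2σ²(1 − r)
- ANCOVA residual: σ²(1 − r²)

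Hence ANCOVA/change = (1 + r)/2 and ANCOVA/final = 1 − r². With SD of change 18.03, the implied score SD is 18.03/√(2(1 − r)).

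**Step 3: power and precision at 39 per arm.** The half-width is 1.99 × SD × √(2/39). The one degree of freedom spent on the covariate is ignored.

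| | r = 0.3 | r = 0.5 | r = 0.7 |
|---|---|---|---|
| ANCOVA/change variance | 0.65 | 0.75 | 0.85 |
| Implied score SD | 15.2 | 18.0 | 23.3 |
| Power at 11.6 points, change score | 80% | 80% | 80% |
| Power at 11.6 points, 12-month score alone | 91% | 80% | 58% |
| Power at 11.6 points, ANCOVA | 94% | 90% | 86% |
| Power at 10 points, change score | 68% | 68% | 68% |
| Power at 10 points, ANCOVA | 85% | 80% | 75% |
| 95% CI half-width, change score | 8.1 | 8.1 | 8.1 |
| 95% CI half-width, ANCOVA | 6.6 | 7.0 | 7.5 |

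**Step 4: relaxing equal SDs.** Let the 12-month SD be k times the baseline SD. In units of the baseline variance, change has variance 1 + k² − 2rk and ANCOVA k²(1 − r²). The ratio ANCOVA/change is:

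| | r = 0.3 | r = 0.5 | r = 0.7 |
|---|---|---|---|
| k = 1.0 | 0.65 | 0.75 | 0.85 |
| k = 1.2 | 0.76 | 0.87 | 0.97 |
| k = 1.4 | 0.84 | 0.94 | 1.00 |

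Change minus ANCOVA variance is (1 − rk)², and final minus ANCOVA variance is r²k². Neither can be negative. So the direction does not depend on the assumptions, but the size does. ANCOVA ties with change scores when rk = 1 and with final scores when r = 0.

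**The case against.** The strongest reply is that the ANOVA is described as running over time and VISA-A is measured at baseline, so the natural reading is a repeated-measures model with baseline as one time level. Baseline then enters by differencing. This stands. A reader might infer from the article that baseline is handled by significance tests alone, or that any chance imbalance passes whole into the primary result. The text does not establish either: the second holds only for a comparison of 12-month scores alone, and the Statistical analyses section does not commit to that. What remains is that the differenced analysis is still, in general, less precise than one with baseline as covariate.

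A reader might also infer bias, an undersized trial, or that adjustment decides whether a 10-point difference can be detected. None of these is supported. All three analyses are unbiased on average under randomisation. The trial has its planned 80% power on its own inputs. An observed 10-point difference would already exclude zero with the change-score half-width of 8.1. At r = 0.3 the gain over 12-month scores alone is only from 91% to 94%.

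A third reply is that an article condenses its source, and the covariates may stand in a fuller plan that is not shown. That is why the point is worded as no adjustment stated, not as adjustment excluded. But the article is not silent: it names a model family and positively prescribes the baseline tests. Nor does it say that covariates would be chosen by baseline p-values, and it should not be charged with that.

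**Conclusion.** The point holds as an efficiency improvement that should be made. The article states no baseline covariate for the primary treatment comparison, and on either reading of its ANOVA the estimate is in general less precise than a baseline-adjusted one, and at best equal to it.

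At r = 0.5 with equal SDs, adjustment removes 25% of the variance under both readings. Across r from 0.3 to 0.7, it adds 6 to 14 percentage points of power over change scores at the planned 11.6 points, and 7 to 17 points at the 10-point minimal important difference. These sizes rest on an assumed r and on equal SDs. With a 12-month SD 1.4 times the baseline SD and r = 0.7, the gain over change scores vanishes.

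The baseline tests are a lesser fault: they inform nothing and correct nothing.

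**What to change.** In Statistical analyses, state the primary estimate as the between-arm difference in VISA-A at 52 weeks, adjusted for baseline VISA-A, from an ANCOVA or from a mixed model over the follow-up visits with baseline VISA-A as covariate. Word the outcome definition to match. Do the same for each continuous secondary outcome that has a baseline value. Replace the baseline significance tests with descriptive statistics by arm.

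The sample size need not change. The cost is wording only: baseline VISA-A is already in the schedule, and no visit, measurement or participant is added. Trial status reports 14 participants included by July 2017, so at that stage the wording could be settled well before unblinding.
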